## 1.0 Background, Objective and Specific Aims

### 1.1.1 Treatment-Resistant Depression (TRD) in Older Adults

Canadians over the age of 65 constitute 13% of the population (4 million); with the aging of the baby-boomers, their number will double over the next 20 years. Depression is the most common, treatable, mental disorder in late life, making it a major public health concern: 2 to 4 % of persons over the age of 65 suffer from major depression. By these estimates, up to 360,000 Canadian adults over the age of 65 will suffer from major depressive disorder. These data predict an epidemic of late-life depression (LLD) that will place tremendous burden on the healthcare system. LLD is also typically complicated by co-morbid medical illness and polypharmacy and it is associated with higher rates of disability and mortality (both from suicide and physical illness). Older adults with depression who suffer a myocardial infarction are four times more likely to die within 4 months than those without depression and the risk of a suicide attempt is double in the elderly compared to younger adults. As a result, LLD is associated with higher rates of healthcare utilization and hospitalization.

Current pharmacological treatments for LLD, however, provide modest efficacy. Rates of treatment resistance in randomized controlled trials (RCT) in LLD range from 55-81% using first line antidepressants. Further, the elderly are more likely to experience relapses and recurrences than younger adults. The failure of first line treatment to induce remission in patients leads to impaired psychosocial function and diminished quality of life.

### 1.1.2 Repetitive Transcranial Magnetic Stimulation in TRD

Repetitive transcranial magnetic stimulation (rTMS) is an emerging treatment for medically refractory major depressive disorder (MDD). rTMS involves direct stimulation of cortical neurons using externally applied, powerful, focused magnetic field pulses. Dozens of studies and several meta-analyses over the last 15 years have shown that rTMS of the dorsolateral prefrontal cortex (DLPFC) produces statistically significant improvements in MDD, even when medications have failed. In the most recent generation of randomized controlled trials, rTMS consistently achieves response rates of 50-55% and remission rates of 30-35% in medically refractory MDD patients.

rTMS has been shown to be effective and well tolerated for depression in younger and older adults. However, early rTMS studies with older adults were limited by suboptimal stimulation parameters, small sample sizes and insufficient treatment durations. A trial of rTMS in LLD with vascular disease found a greater remission rate with active compared to sham^38.

The optimal parameters for rTMS are still in the process of being established, however the most widely-used rTMS protocols apply excitatory, 10 Hz stimulation to the left DLPFC; high frequency left (HFL) or inhibitory, 1 Hz stimulation to the right DLPFC; low frequency right (LFR), or both. Our group has studied rTMS in 43 patients with treatment resistant late-life depression (TRLTD) over two separate studies and have found superior remission rates with bilateral stimulation (40%) compared to both unilateral (0%) and sham (0%) stimulation ( $\chi^2 = 11.30$  df, 2;  $p = .004$ ). Further evidence supporting the use of bilateral stimulation comes from another randomized control trial (RCT) conducted by our group, that assesses the efficacy of deep rTMS in

[figure not shown]

more than 60 patients (NCT01860157). The coil used in this study also has a bilateral electric field distribution. An interim analysis demonstrates superiority of the active over placebo stimulation. However, this device is not capable of “brief patterned” forms of stimulation.

### 1.1.3 Accelerated rTMS Protocols

Newer rTMS protocols that use “patterned” bursts of stimulation can achieve similar or more potent effects on synaptic facilitation or inhibition using markedly fewer pulses, applied over 1/10 the time of the standard form of treatment. The most widely studied brief protocol is theta-burst stimulation (TBS). A blinded analysis of our multicenter non-inferiority trial (NCT01887782) demonstrates non-inferiority of intermittent TBS compared to the standard 3000 pulses FDA approved protocol in 340 younger adults with depression.

Unlike conventional stimulation, TBS mimics the endogenous theta rhythms of the brain, and this is thought to explain its greater potency in inducing long-term potentiation of synaptic connections in the target region. For example, 600 pulses of continuous TBS, applied over a period of 40 s, produces more powerful and longer-lasting inhibitory effects than 900 pulses of 1 Hz over a period of 15 minutes. Likewise, 600 pulses of intermittent TBS, applied with a duty cycle of 2 s on, 8 s off, produced more powerful and longer-lasting excitatory effects than any other protocol studied in a 6-way comparison against conventional protocols.

Conventional rTMS protocols, as used in the major trials in the USA that secured FDA approval in 2008, applied 3000 pulses of unpatterned, 10 Hz stimulation administered over 37.5 minutes. These protocols limit the number of patients who can be treated with a single machine to around 10 per day, thus perpetuating the high cost of treatment. In contrast, the TBS protocols that have been shown effective in MDD require as little as 1-3 minutes. If shown to have non-inferior efficacy to conventional rTMS in TRLLD, these would allow for the treatment of 4-5 times as many patients per device (including turnover time), with fewer pulses of stimulation, thus reducing overall costs by a proportionate amount.

### 1.2.0 Predicting Treatment Response: Network Connectivity

Predicting response to treatment in TRLLD may have an even greater impact on outcomes than reducing the cost through TBS. Depression in older adults, and non-response to antidepressants, is associated with low connectivity in the cognitive control network (CCN). This network has a bilateral DLPFC distribution and is precisely the target of our stimulation protocol. Data from the resting state fMRI (rs-fMRI) of our non-inferiority trial suggests low connectivity in the left CCN at baseline predicts response to rTMS. This provides evidence that rTMS could potentially target the underlying network dysfunction in older adults and that using advanced imaging predicting tools could identify those most likely to benefit.

### 1.3.0 Individual-Level Prediction of Outcomes: Role of Automated Classifiers

Over two decades of neuroimaging literature are available comparing patients with MDD to healthy controls, or treatment responders to non-responders, at the group level. The most recent studies in this

[figure not shown]

literature have also begun to identify differential predictors of outcome for two types of intervention, such as pharmacotherapy versus psychotherapy. However, while group-level comparisons can be revealing about the general mechanisms of MDD and its various treatments, they unfortunately do not address the much more challenging problem of classifying *individual subjects* according to disease state or treatment response, in an accurate and replicable manner. Solving this problem is a crucial prerequisite for translation of predictive neuroimaging into clinical use.

Only recently has the literature begun to attempt classification of subjects at the individual level. There are a wide variety of machine learning techniques now in use to solve individual-level classification and prediction problems on high-dimensional neuroimaging datasets, including Bayesian multitask learning, Gaussian process classification, and support vector machines (SVM). The latter approach is the most widely used to date for disease state prediction.

Support vector machines (SVM) have been applied to rs-fMRI data to distinguish MDD patients with healthy controls at 95% accuracy using functional connectivity between pre-selected anatomical regions and at 94.3% accuracy and 100% positive predictive value using whole-brain functional connectivity. Other authors have improved classifier performance to >99% accuracy by applying graph theoretical metrics (such as modularity, participation index, or clustering coefficient) to the whole-brain functional connectivity data. Similar approaches have been used to distinguish schizophrenia patients from healthy controls at 93.2% accuracy.

Although these figures are encouraging, it should be noted that these studies all trained their classifiers on relatively small datasets of 20-30 individuals per group, and none of them tested the performance of the models on a second replication dataset; hence, the reliability and generalizability of this approach remains unproven. One of the few studies to use a large training set (n=238) as well as replication datasets achieved 91% accuracy in classifying rs-fMRI scans as belonging to either children age 7-11 or adults age 24-30, with 92% and 93% accuracy on 2 replication datasets of sizes n=195 and n=186, suggesting that good replicability can be achieved if the training set is sufficiently large.

#### 1.4.0 Objectives and Hypotheses

In summary, TBS has been shown to be effective in open-label studies of major depression. It has also been shown to have greater potency than conventional protocols in studies of motor physiology. However, to date there has been no direct comparison of the relative efficacy of these different forms of rTMS for TRLLD under randomized controlled conditions. This study will address the question of the relative efficacy of conventional versus theta-burst stimulation in the setting of TRLLD by comparing conventional HFL rTMS to TBS, while training and validating classifier algorithms for predicting treatment response using rs-fMRI.

[figure not shown]

**Objective 1:** To compare the effectiveness of a course of 4 minute sessions of TBS to a course of 45 minute sessions of conventional rTMS in LLD.

**Hypothesis 1:** Sequential bilateral forms of TBS will have non-inferior effectiveness compared to sequential bilateral conventional rTMS in older adults with depression.

**Objective 2:** To determine if an automated classifier can use pre-treatment resting-state fMRI, clinical and cognitive data to predict treatment outcome for both TBS and conventional rTMS.

**Hypothesis 2:** Patterns from whole-brain functional connectivity, obtained from pre-treatment rs-fMRI, will distinguish responders and nonresponders with >85% accuracy for TBS and standard rTMS.

**Exploratory Objective 1:** To compare network connectivity in depressed adults across the lifespan and rTMS-induced changes between bilateral and unilateral stimulation approaches using existing unilateral data in adults <60 from our group.

## 2.0 Significance

If the study hypothesis is confirmed, the implication will be that rTMS can maintain or better its current levels of efficacy using treatment protocols that can be completed in 1/10 the time of the standard form of treatment. An 8-minute treatment protocol would allow for up to 40 patients to be treated per rTMS device per day, and with a 4 week treatment protocol this would imply a capacity of nearly 500 patients per device per year. The cost of rTMS per patient could also be reduced proportionately.

In future treatment, a reliable pre-treatment fMRI test could spare non-responders from futile treatment while offering a recommendation for patients with favorable network activity patterns on fMRI. If fully implemented, this would boost the percentage of successful outcomes to 90% response and 60% remission *among treated patients*. In health-economics terms, this would reduce the cost per response. Given that responder and remitter patients would be more likely to return to work and less likely to require long-term disability support, rTMS could potentially have a positive impact on both the overall rates of treatment-resistant depression and on the significant social, economic, and health costs of the disease itself.

Our proposed trial will be large enough to demonstrate non-inferiority of TBS compared to standard rTMS, while training and validating classifier algorithms for predicting treatment response using rs-fMRI. These objectives, if realized, would yield a direct and near-term payoff in terms of outcomes and socioeconomic burden for the growing number of older adults with depression.

## 3.0 RESEARCH DESIGN AND METHODS

### 3.1.1 Research Design and Methods

Up to 220 outpatients at the University Health Network and the Centre for Addiction and Mental Health, meeting diagnostic criteria for unipolar major depressive disorder, will be randomized to receive conventional 1 Hz rTMS to the right DLPFC followed by 10Hz rTMS to the left DLPFC, or continuous theta-burst stimulation (cTBS) to the right DLPFC followed by left DLPFC intermittent theta-burst stimulation (iTBS), with rs-fMRI obtained before and after treatment. We have chosen a non-inferiority study design to align with the hypothesis of the study that TBS will be no different in terms of clinical outcome but faster and more efficient.

[figure not shown]

Following randomization, patients will undergo a series of clinical and cognitive assessments as well as an MRI (60 minute) and motor threshold testing to determine the appropriate site and strength of stimulation according to standard methods, and then begin treatment. If a participant is able to have an MRI but cannot tolerate the MRI, e.g. due to claustrophobia, they will still be allowed to undergo treatment using an approximated method called beam F3. This method targets the exact same neuronavigated target and has been shown to be within 3 millimeters of the neuronavigated site. The treatment phase will last between four and six weeks. Treatment will be administered daily, 5 days per week (i.e., 20-30 treatments). Participants will be permitted to miss scheduled treatment days due to illness or scheduling conflicts. They will still receive the entire 20-30 treatments, but over a longer time period (i.e. greater than 4-6 weeks). However, those who miss more than 3 consecutive treatment days will be excluded from the study as it is our intention to encourage the commitment of the participants in the study as well as discourage prolonged duration of time taken to complete the protocol as it could affect the efficacy of the treatment. All missed treatment days will be recorded in a log for each participant.

Depressive symptoms will be assessed using the clinician-rated Montgomery Asberg Depression Rating Scale (MADRS), the 17-Item Hamilton Depression Rating Scale (HRSD-17), and the self-rated 16-item Quick Inventory of Depressive Symptoms (QIDS16). Change in scores on the MADRS, from baseline to endpoint, will be the primary clinical outcome of interest. The primary neuroimaging outcome measure will be the whole-brain functional connectivity on rs-fMRI. If the subject experiences an improvement in their symptoms by a minimum of 30% based on the change in MADRS score from baseline to week 4, they will receive an additional 10 treatments over the course of 2 weeks in an attempt to optimize treatment response. Those subjects that do not achieve a 30% reduction by week 4 will be given the opportunity to continue for 2 more weeks as they may be late responders and benefit from the additional 10 treatments. All participants will undergo a post-treatment MRI scan after they complete treatment. Participants who are in remission at weeks 3 and 4 will exit the study at week 4 and undergo a post-treatment MRI scan. For participants who do not wish to continue past week 4 they will undergo a post-treatment MRI scan (30 minutes) and complete all final visit measures.

An independent, trained rater at each site will administer the clinical assessment scales at baseline, after each 5 sessions of treatment, and at 1, 4, and 12 weeks post-treatment. Cognitive assessments will be administered at baseline, after the final treatment session (including at drop-out), and at 12 weeks following the final treatment. These assessments can be done within 1-2 days of the scheduled time point. The independent raters will be blinded to the treatment being administered. All treatments will be conducted with minimization of personal contact (i.e., verbal communication) with the subject to reduce the impact of nonspecific therapeutic contact on outcomes. Patients who participate in the study will not be allowed to meet with each other before, during and after assessment or treatments in order to maintain the blind. Patients will be discontinued if they experience worsening in depression, where worsening of depression is defined as an increase in MADRS from baseline of more than 25% during two consecutive assessments, or development of active suicidal intent or attempted suicide.

Up to 90 healthy controls, age 60 and older, will undergo one MRI and cognitive assessments to serve as a comparative group for the study. All healthy controls will undergo a screening visit to assess eligibility. This will include assessment for psychiatric disorders with the MINI 6.0, current depressive symptoms as assessed by the MADRS, as well as current medications and a medical history using the CIRS-G. If eligible, controls will

[figure not shown]

complete the same cognitive assessment battery as participants and will undergo a one hour MRI scan at Toronto Western Hospital.

Subjects will be reimbursed \$150 total for the two MRI scans and as a partial contribution towards transportation, meals, time, etc. associated with their participation in the study. If subjects do not complete the second MRI they will receive \$75 for their participation. Healthy controls will be reimbursed \$150 for their one MRI as it is 1 hour in length and as a partial contribution towards transportation, meals, time, etc. associated with their participation in the study. They will also be reimbursed \$10/hr for the cognitive assessments.

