### 3.1.4 Randomization and Blinding

Subjects will be randomized into the study, stratified by severity of treatment resistance (failure > 1 adequate trial). Degree of treatment resistance has been a major predictor of response to treatment in prior rTMS trials and it is essential to ensure that the groups are balanced with respect to this variable. The ATHF is a validated and reliable method of assessing adequacy of prior antidepressant treatment. We will also stratify the randomization by sites to ensure balance in the treatment condition across the two sites. We will randomize subjects based on a stratified randomization scheme using a random permuted block method. As the difference in duration between standard rTMS and TBS protocols is critical to the rationale of the study, it is not possible to blind the rTMS technicians or the patients to treatment assignment; however, since we believe there is equipoise between the two treatments and explain this to patients the expectancy effects should be minimal. **Raters** obtaining outcome measures **will be blind** to treatment assignment. All treatments will be conducted with minimization of personal contact (i.e., verbal communication) with the subject to reduce the impact of nonspecific therapeutic contact on outcomes.

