#### Clinical Assessments During and After Treatment:

Clinical outcome measures will be assessed in the week prior to treatment, after each 5 sessions of treatment, then at 1, 4, and 12 weeks after treatment. These assessments can be completed over the phone if the participant is unable to attend the visit within the given time frame. The MADRS will be the primary

[figure not shown]

outcome measure and a score of greater than or equal to 18 will be used to establish eligibility. The HDRS-17 is the most commonly used outcome measure in previous randomized trials of rTMS and will be included for comparison purposes. However, the MADRS is well validated in LLD and has been used in trials of other interventions in TRLLD and will therefore be the primary measure. Secondary outcome measures will include the HDRS-17 and the self-rated QIDS16. The BSS will be administered after each 5 sessions of treatment, then at 1, 4, and 12 weeks post treatment as a safety measure to assess for suicidality.

To assess other potential predictors of response of rTMS we will assess anxiety, quality of life and medical burden. We will use the Brief Symptom Inventory – Anxiety, the Quality of Life Enjoyment and Satisfaction Scale (Q-LES-Q), and the Cumulative Illness Rating Scale for Geriatrics (CIRS-G).

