## **3.1.6 Interventions**

### *rTMS Treatment Procedures*

Following randomization and baseline MRI, patients will undergo neuronavigation, the target location will be specified by reverse coregistration from a stereotaxic coordinate on the standard Montreal neurological Institute (MNI-152) template brain, on to each individual's anatomical MRI. The MNI coordinates for L and R DLPFC will be [ $\pm 38$  y+44 z+26], drawn from a study identifying this site as optimal based on clinical outcomes and resting-state functional connectivity. rTMS will employ the MagPro X100/R30 stimulator equipped with the B70 fluid-cooled coil for DLPFC stimulation (MagVenture, Farum, Denmark). Neuronavigation will proceed using the *Visor 2* system (Advanced Neuro Therapeutics, Madison, WI) to position the coil for maximal field

[figure not shown]

strength at the left and right target region of the DLPFC for each individual subject. If a participant was unable to complete the MRI they are still able to undergo treatment using beam F3.

Prior to the first treatment, each subject's motor threshold (MT) will first be determined according to published methods during neuronavigated TMS over the primary motor cortex. Subjects will then undergo 20-30 sessions of rTMS, once daily on weekdays for 4 to 6 weeks. One study arm will undergo conventional sequential bilateral rTMS: R DLPFC stimulation at 120% resting motor threshold (RMT) at 1 Hz, in one train of 600 pulses over 10 min, followed by L DLPFC stimulation at 120% of RMT, at 10 Hz, in trains of 4 s with 26 s intertrain interval, for a total of 3000 pulses over 37.5 min. The second study arm will undergo cTBS of the R DLPFC at 120% RMT using bursts of 3 pulses at 50 Hz, bursts repeated at 5 Hz for a total of 600 pulses over 40 seconds, followed by iTBS of the L DLPFC at 120% RMT using bursts of 3 pulses at 50 Hz, bursts repeated at 5 Hz with a duty cycle of 2 s on, 8 s off for a total of 600 pulses over 3 min 9 s. Participants will be titrated to 120% RMT within the first four treatments to aid with tolerability. Subjects who cannot be titrated within 4 days will be allowed to continue in the study but the amount of time to reach the target intensity will be recorded in the treatment logs.

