### 3.2.3 Outcome Analysis

**Objective#1:** Assessing non-inferiority of bilateral TBS based on change on the MADRS, an ANCOVA covarying for baseline differences will be used to measure the change at the final time point for each subject. This will be the primary clinical outcome measure.

Secondary outcome measures will include change from baseline to endpoint on the HDRS-17 and response and remission on the HDRS-17 and MADRS.

For categorical outcome measures, response will be defined as  $\geq 50\%$  reduction in symptoms on the HDRS-17. Remission will be defined as a HDRS-17  $\leq 10$  and a MADRS  $\leq 10$  at the week 4 or 6 final time point. Other secondary outcome measures will explore comparison of side effects between the two treatment arms, anxiety scales, quality of life scales and cognitive measures.

**Objective#2:** Outcome prediction from whole-brain rs-fMRI scans, data will be analysed using the FSL platform and in-house scripts to extract whole-brain regional connectivity matrices, followed by automated classifier training, using a support vector machine approach according to previously reported methodology. Based on preliminary data, classifiers will be trained on 4 features: whole-brain functional connectivity, region-wise betweenness centrality, and edge-wise functional connectivity variability. Automated classifiers will be trained and tested on the datasets for standard bilateral groups, with iterative cross-validation to ensure generalizability.

[figure not shown]

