**Table 1. Schedule of Events**

| Clinical and Cognitive Assessments* | Screening and Baseline | Acute Phase:
Daily TBS or HFL rTMS             |                                     | Follow-up Assessments                           |                                            |
|-------------------------------------|------------------------|---------------------------------------------------|-------------------------------------|-------------------------------------------------|--------------------------------------------|
|                                     | Week 0                 | Weeks 1–3 (4&5 if responder) after every 5 visits | Final Visit: Week 4 or 6 or Dropout | 1 and 4 weeks following final treatment session | 12 weeks following final treatment session |
| MINI                                | X                      |                                                   |                                     |                                                 |                                            |
| TASS                                | X                      |                                                   |                                     |                                                 |                                            |
| SBT                                 | X                      |                                                   |                                     |                                                 |                                            |
| MoCA                                | X                      |                                                   | X                                   |                                                 | X                                          |
| BSI-Anxiety                         | X                      |                                                   | X                                   |                                                 | X                                          |
| ATHF                                | X                      |                                                   |                                     |                                                 |                                            |

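### Pre-treatment ratings are placed after randomisation in a trial whose patients cannot be blinded; the arm is not withheld until they are done and the baseline MADRS for the ANCOVA is not identified

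*Protocol*

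**What the plan says.** Section 3.1.1 gives the order of events: "Following randomization, patients will undergo a series of clinical and cognitive assessments as well as an MRI (60 minute) and motor threshold testing", after which treatment begins. Section 3.1.4 says that "it is not possible to blind the rTMS technicians or the patients to treatment assignment", because session length differs between the arms. Raters are protected: "The independent raters will be blinded to the treatment being administered" (3.1.1).

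Other places bear on when baseline is taken, but none settles it:

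- Section 3.1.5, on clinical assessments: "Clinical outcome measures will be assessed in the week prior to treatment". This ties the ratings to the start of treatment and does not mention randomisation.
- The same subsection makes the MADRS the primary "outcome measure and a score of greater than or equal to 18 will be used to establish eligibility". Section 3.1.2 lists that threshold as an inclusion criterion.
- Section 3.1.6: "Following randomization and baseline MRI, patients will undergo neuronavigation". Both events precede neuronavigation, but their order relative to each other is left open.
- Table 1 has a single "Screening and Baseline" column at Week 0, holding the MADRS, HRSD-17, QIDS-16, cognitive tests and MRI. Randomisation is not marked.

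The primary analysis in section 3.2.3 is "an ANCOVA covarying for baseline differences will be used to measure the change at the final time point for each subject".

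**The concern.** An ANCOVA covariate should be a quantity that allocation cannot affect. If a patient knows the arm when the baseline rating is taken, disappointment or enthusiasm can alter what is reported. The self-rated QIDS-16 has no protection against this. The MADRS and HRSD-17 have partial protection, since a blinded rater still scores what an unblinded patient says.

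The baseline MADRS enters both the primary outcome, as change from baseline, and its adjustment. It is also the reference for the 30% improvement and 25% worsening thresholds in section 3.1.1. An arm difference in baseline reporting could therefore move a non-inferiority contrast judged against a margin of 2.75 points.

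There is a second, simpler consequence. With the assessments placed between randomisation and treatment, a patient who withdraws in that interval is a randomised loss, and may have no baseline for scales that are not entry criteria.

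**Working it through.** **Order of events.** Section 3.1.1 is the only text that orders the clinical and cognitive assessments relative to randomisation, and it puts them after it. At least one MADRS must come before randomisation, because a score of 18 or more is an entry criterion. However, the list of patient screening instruments in section 3.1.5 does not include the MADRS, and section 3.2.3 does not say which score is the covariate. HRSD-17, QIDS-16, Q-LES-Q, BSI-Anxiety and the cognitive battery are not entry criteria, so nothing in the protocol requires a pre-randomisation value for them. No section says when patients are told their arm.

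**The plan's own figure.** Inputs from section 3.2.1: margin 2.75, SD of change 7.8, significance 0.05, power 80%. With a true difference of zero and a one-sided 0.05 test:

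n per arm = 2 × (1.645 + 0.842)² × 7.8² / 2.75² ≈ 99.5, so 100.

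This matches the stated 100 per arm (200 in total). One-sided 0.025 would give 127 per arm, so the plan's number implies one-sided 0.05, which is used below.

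**Illustration of size.** The shifts and slopes here are assumptions; the documents give neither.

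- Standard error of the contrast: 7.8 × √(2/100) = 1.103. The SD of change stands in for the ANCOVA residual SD.
- Let b be the arm difference in reporting at baseline, e the same at endpoint, and β the slope of endpoint on baseline. The bias in the adjusted contrast is e − βb.
- Take b = 1, e = 0, β = 0.5. The size of the bias is 0.5 × 1 = 0.5 points, and 0.5 / 2.75 = 18% of the margin.
- If it favours TBS, one-sided error at the margin is Φ(0.5/1.103 − 1.645) = Φ(−1.192) = 11.7%, against a nominal 5%.
- If it goes against TBS, power is Φ((2.75 − 0.5)/1.103 − 1.645) = Φ(0.395) = 65%, against 80%.

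Range with e = 0:

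| Baseline shift b | Slope β | Bias | Share of margin | Error if it favours TBS | Power if against TBS |
|---|---|---|---|---|---|
| 0.5 | 0.3 | 0.15 | 5% | 6.6% | 76% |
| 1 | 0.3 | 0.30 | 11% | 8.5% | 72% |
| 1 | 0.5 | 0.50 | 18% | 11.7% | 65% |
| 1 | 0.7 | 0.70 | 25% | 15.6% | 58% |
| 2 | 0.7 | 1.40 | 51% | 35% | 34% |

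**The case against.** A reader might infer that the primary covariate, and the baseline of every change score, is certainly measured after patients know their arm. The documents do not support that. They never say when the arm is disclosed, the eligibility MADRS precedes randomisation and could be the analysis baseline, and Table 1 merges screening with baseline. Which MADRS record is used may also be fixed in a statistical analysis plan that is not at hand. What stands is that the protocol itself states an order, the order is the unsafe one, and nothing in the protocol offsets it.

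A reader might also infer that patients who fail the MRI step are lost after randomisation. Sections 3.1.1 and 3.1.6 say otherwise: those who cannot tolerate the scan are still treated, with the beam F3 method. Nor is there a plausible route by which knowing the arm would bias resting-state connectivity.

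Blinded raters limit the effect on the primary scale. Section 3.1.4 argues that expectancy should be minimal because equipoise is explained to patients. That is reasonable, but it is an expectation rather than a safeguard.

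The strongest objection concerns the arithmetic, which assumes a shift present at baseline and gone by endpoint. Patients stay unblinded throughout. If a 1-point shift persists, the bias with a post-randomisation baseline is 1 − 0.5 = 0.5 points at slope 0.5, and with a clean baseline it is the full 1 point. This is correct, so the figures are illustrative only. It does not justify the present order: endpoint reporting bias comes from open treatment, and a contaminated covariate offsets it only by accident.

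**Conclusion.** The point holds as a weakness of stated order combined with missing definitions, not as proof of a biased primary covariate. Section 3.1.1 puts the pre-treatment clinical and cognitive assessments after randomisation, patients cannot be blinded, and the protocol neither conceals the arm until those assessments are complete nor identifies the baseline MADRS. Exposure is greatest for the QIDS-16 and smaller for the MADRS and HRSD-17.

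On the central assumptions (1-point shift, absent at endpoint, slope 0.5) the bias is 0.5 points and one-sided error is about 12%. The true effect could be nil. A larger figure, such as 23% from a full 1-point bias, would at this shift require an unadjusted change score, which is not the planned analysis. The point deserves correction because the remedy is nearly free.

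**What to change.** In sections 3.1.1 and 3.1.6, state that all baseline ratings and the cognitive battery are completed and locked before randomisation and, where practical, the MRI (or its documented failure) and motor threshold as well. If logistics prevent this, state that the arm is not disclosed until they are complete.

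Define the ANCOVA baseline in section 3.2.3 as the last MADRS before randomisation. Align the assessment timing in section 3.1.5 and the wording in section 3.1.6 with this, and mark randomisation in Table 1.

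The cost is protocol wording and randomisation a few days later. The sample size is unchanged, and fewer patients should be lost between randomisation and first treatment, which helps preserve the 10% attrition allowance. The change removes allocation-driven bias at baseline only; bias in endpoint reporting by unblinded patients remains.
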